#### 4. Asthma severity, defined as use of asthma preventer medication at five years of age

**Positive** (Severe asthma) if in the 5-year questionnaire the parent/guardian reports that the child has used a preventer medication in the last 12 months (with or without use of a reliever medication).

**Negative** (mild or no asthma) if in the 5-year questionnaire

- the parent/guardian reports that the child has not used any preventer medication in the last 12 months
- OR
- responded 'no' to ISAAC Q1 and ISAAC Q6.

**Missing** if the asthma medication section of the 5-year questionnaire was not completed

OR

The participant does not fulfil the 'positive' or 'negative' criteria above.

## 5. STATISTICAL METHODOLOGY

### 5.1. GENERAL METHODOLOGY

Although the details of the randomisation groups have already been unblinded (to the trial statisticians and specific data managers/trial co-ordinators) and the results published for Part 1 of the study, the PIs, as well as individuals responsible for cleaning and preparing the data for Part 2 have remained blinded. The data will only be fully unblinded once the database has been locked and all the SAPs have been finalised, approved by the PIs and made publicly available.

The primary outcome will be considered in evaluating the effectiveness of the trial intervention at reducing incidence of asthma. The magnitude of the treatment effect, with 95% confidence intervals and p-value, will be estimated for the outcome.

## 5.2. DESCRIPTIVE STATISTICS

### 5.2.1. PARTICIPANT DISPOSITION

All participants who were invited to participate in MIS BAIR will be accounted for in the CONSORT diagram. The CONSORT diagram for Part 1 has already been published , and will be updated to include Part 2. The number and proportion of participants who did not consent to Part 2 and withdrew from the study will be presented by intervention group (BCG or no BCG). The number and proportion of respondents to the asthma section of the five-year questionnaire will also be presented by intervention group.

### 5.2.2. PARTICIPANT CHARACTERISTICS

The demographic characteristics of the participants (including infant, maternal, paternal and environmental factors) at randomisation in the ITT population will be presented for each intervention group (BCG or no BCG) using the mean and standard deviation (SD) or median and interquartile range (IQR) for continuous and using numbers and proportions for categorical data. Environmental factors that may change over time may also be presented at one year and five years of age and 'ever' exposed (Any exposure between zero to five years). The full list of demographic characteristics that may be included is shown in *Appendix 1*. Given most of these data are already published , discretion will be used in determining which variables to include in publications.

Participant characteristics at baseline, one year and five years for the subset of participants who consented to Part 2, and for the subset of participants who answered the asthma questions in the 5-year questionnaire, will be also be presented.

### 5.2.3. HANDLING OF MISSING DATA

#### **Missing data for environmental exposures**

To determine whether a participant has 'ever' been exposed to an environmental exposure such as smoking or pets, missing values will be treated as '0' (no), provided that the participant responded 'no' in any completed questionnaires and that the baseline and five-year questionnaires are complete. This relies on the assumption that it is unlikely that a household member will become a smoker and then stop again, and similarly it is unlikely that the household will acquire a dog or cat for a short period of time.

#### **Multiple Imputation**

The primary analysis will be an intention-to-treat analysis. It is already known that the proportion of missing data for the primary outcome will be more than 5%, due to loss to follow-up. To adjust for this selection bias (collider stratification bias), multiple imputation models will be conducted for the outcome variables and 50 completed data sets will be imputed by chained equations including all the children initially randomised. The primary outcome, strata variable (mode of birth: vaginal/caesarean), and the variables associated with either remaining in the study or asthma listed below will be included in the imputation model. Although there are two other randomisation strata (study site and singleton/twin), the number of participants recruited at study sites other than the Mercy, and the number of twins, is so small that it is not possible to multiply impute separately for these strata.

The directed acyclic graph (DAG) below summarizes the expected associations between variables, including the open front door path created by restriction on the collider 'remain in the study' caused by loss to follow-up and incomplete data. The multiple imputation aims to impute the missing data for those who did not remain in the study. By including variables that are expected to be associated with both remaining in the study and the outcome, the restriction on 'remain in the study' is removed and this open path is closed.

[figure not shown]

Informed by the DAG, and in order of priority, the variables listed below may be included in the multiple imputation. If necessary, the number of categories included in categorical variables will be reduced to allow the multiple imputation to run.

| Variable                        |                        | Definition                                                                                                                                                                                    |
|---------------------------------|------------------------|-----------------------------------------------------------------------------------------------------------------------------------------------------------------------------------------------|
| Maternal education              | Generated, categorical | Three categories – below year 10, year 12/trade certificate or university educated.                                                                                                           |
| Daycare attendance  | Generated, binary      | Positive if the participant had a sibling in daycare at birth or during the first year of life, or if the participant attended any daycare in the first year of life.                         |
| Smoke exposure      | Generated, binary      | Positive if mother smoked in pregnancy or if there was ever a smoker living in the house on any questionnaire. Negative, if there is no evidence of smoking at any time point (no or missing) |
| Sex                 | Raw, binary            | Assigned male or female at birth                                                                                                                                                       |

|                                                                                                 |                        |                                                                                                                                                                                                                                                                                |
|-------------------------------------------------------------------------------------------------|------------------------|--------------------------------------------------------------------------------------------------------------------------------------------------------------------------------------------------------------------------------------------------------------------------------|
| Breastfeeding duration                                                              | Generated, categorical | No breastfeeding, <1 week, 1 wk – 3 months, 3-6 months, 6-12 months, >12 months                                                                                                                                                                                                |
| Family history of asthma                                                            | Generated, binary      | Positive if mother, father or sibling has asthma                                                                                                                                                                                                                               |
| Pet ownership at birth                                                             | Generated, binary      | Positive, if the family had a pet with hair at randomisation (e.g., dog, cat, rabbit, cow)                                                                                                                                                                                     |
| Delivery mode                                                                       | Raw, binary            | Vaginal or caesarean birth                                                                                                                                                                                                                                                     |
| Season of birth                                                                    | Generated, categorical | Categories of birth based on season (Spring (Sept – Oct), Summer (Nov - Jan), Autumn (Feb – May), Winter (Jun – Aug))                                                                                                                                                          |
| Maternal age at birth of participant                                               | Raw, continuous        | Age in years                                                                                                                                                                                                                                                                   |
| Paternal age at birth of participant                                               | Raw, continuous        | Age in years                                                                                                                                                                                                                                                                   |
| Low birthweight                                                                    | Generated, binary      | Low birthweight is <2500g                                                                                                                                                                                                                                                      |
| Timing of recruitment                                                                           | Generated, categorical | Categories determined based on date of recruitment.                                                                                                                                                                                                                            |
| Evidence of asthma                                                                 | Generated, binary      | Positive if parent reported asthma or wheeze disturbing sleep or exercise at 36 or 48 months or said yes on the follow-up questionnaire. Negative if completed the 36 and 48 month questionnaires and did not report those symptoms or said no on the follow-up questionnaire. |
| Hospitalisation for bronchiolitis in the first year of life                        | Generated, binary      | Positive if parent reports hospitalisation for bronchiolitis in the first year of life. Negative if all 3 month, 6 month, 9 month and 12 month questionnaires were complete and no hospitalisation for bronchiolitis was reported.                                             |
| Atopy (eczema  or atopic sensitization  ) at one year of age | Generated, binary      | Positive if positive for either eczema or atopic sensitisation at one year of age. Negative if negative for both eczema and atopic sensitisation at one year of age.                                                                                                           |

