## 2. BACKGROUND/INTRODUCTION

### 2.1. STUDY DESIGN

MIS BAIR is a phase III, randomised, controlled trial in infants to determine if the bacille Calmette-Guérin (BCG) vaccine reduces the incidence of eczema, allergies, infections and asthma in the first five years of life.

Infants were recruited at Mercy Hospital for Women, Werribee Mercy, Geelong Hospital, St John of God and Murdoch Children's Research Institute in Melbourne over a three-year period from August 2013 to September 2016. At trial design we planned to randomise 1,438 infants 1:1 to receive the BCG vaccine or no vaccine. However, recruitment to the study was stopped before this number was reached as the BCG-Denmark vaccine became unavailable due to a worldwide shortage. The actual number randomised was 1272. Infants were randomised within ten days of birth.

The study involved two parts:

Part 1 – From birth to one year of age

Part 2 – From one to five years of age

At the 1-year MIS BAIR visit participants were asked to re-consent if they wished to continue into Part 2 of the study. For those families who had not been consented at the 1-year MIS BAIR visit, had not verbally declined participation and had given consent to be contacted for future studies, an invitation letter and the PICF were sent to them by email, post or through REDCap and they could consent by post, on REDCap or in person (e.g. at a study visit). Of the 1272 in Part 1, 1027 consented to continue into Part 2.

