## 2.3. STUDY POPULATION

1,272 healthy newborns were randomised, within 10 days of birth, in a 1:1 ratio, to study group 1 (BCG, n=637) or study group 2 (no BCG, n=635). Twin pairs were randomised to the same group but only one twin from each pair was included as a study participant, regardless of birth order. A total of 21 sets of twins were randomised in the trial and 17 sets of twins continued into Part 2.

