### **5.3. PRIMARY DATA ANALYSES**

The percentage of 'asthma ever' reported at five years will be presented separately for children in the treatment and non-treatment groups. Comparison between the treatment arms will be estimated using binary regression adjusted for the randomisation stratification factor of birth mode. Results will be presented as adjusted risk difference and its 95% confidence interval (CI). The analysis will be presented as ITT with multiple imputation as described above.

The two other stratification factors used for randomisation (site and plurality) will not be included in adjustments because it is already known from Part 1 that 98.3% of infants were singleton and 95.2% were from the same site .

As a sensitivity analysis, the same binary regression model will be re-run excluding the 7-10 year follow-up questionnaire data.

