### **5.4. SECONDARY DATA ANALYSES**

For each secondary outcome, the percentage of study participants with the outcome will be presented separately for children in the treatment and non-treatment groups. Comparison between the treatment arms will be estimated using binary regression adjusted for the randomisation stratification factor of birth mode. Results will be presented as adjusted risk difference and its 95% confidence interval (CI).

Intention to treat analysis with multiple imputation will be used for all the secondary outcomes.

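### The imputation model set out in SAP 5.2.3 does not name randomised group; run as listed, it would pull the primary risk difference toward zero by up to the fraction of outcomes missing

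*SAP*

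**What the plan says.** - Section 5.2.3 (Multiple Imputation) plans chained equations on the whole randomised set: "50 completed data sets will be imputed by chained equations including all the children initially randomised".
- The same paragraph gives the content of the model: "The primary outcome, strata variable (mode of birth: vaginal/caesarean), and the variables associated with either remaining in the study or asthma listed below". It then explains why two other randomisation strata, site and plurality, are left out. It does not mention allocation.
- The table of variables is introduced by "Informed by the DAG, and in order of priority, the variables listed below may be included in the multiple imputation". It has 16 rows, from maternal education to atopy at one year. Delivery mode is one of them; randomised group is not.
- On the amount of missing data: "It is already known that the proportion of missing data for the primary outcome will be more than 5%, due to loss to follow-up". No other figure is given for the primary outcome. Section 2.1 adds: "Of the 1272 in Part 1, 1027 consented to continue into Part 2".
- Section 5.3 compares the arms by binary regression adjusted for birth mode, and reports a risk difference: "The analysis will be presented as ITT with multiple imputation as described above".
- Section 5.4: "Intention to treat analysis with multiple imputation will be used for all the secondary outcomes". Section 5.2.4 fits intervention-by-subgroup interactions, also on the imputed data.

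**The concern.** The imputation model should contain at least the terms of the analysis model. Here the analysis model is outcome on BCG plus birth mode, and the imputation model as written lacks the BCG term. A programmer who follows 5.2.3 literally would fill in missing outcomes in both arms from one model that ignores allocation. The completed data would then mix observed children, who show the full effect, with imputed children, who show little of it.

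In a superiority trial this works against the hypothesis under test, and a real benefit could be reported as absent. The same imputations feed the secondary outcomes and the subgroup interactions. The one sensitivity analysis in 5.3 drops the 7-10 year questionnaire data. No complete-case analysis is specified that would reveal the shrinkage.

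**Working it through.** **Inputs.**
- Arms: "study group 1 (BCG, n=637) or study group 2 (no BCG, n=635"), total 1272; about 636 per arm is used below (SAP 2.3).
- Target effect: 22% to 16%, a risk difference (RD) of -6 points (SAP 2.4).
- Fraction missing, f: more than 5% (SAP 5.2.3). Not in Part 2: (1272 - 1027)/1272 = 245/1272 = 19.3% (SAP 2.1). The 30% value is an illustration.
- Assumed: two-sided 0.05, and outcomes missing completely at random.

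**The plan's own figure.** 1438 x 0.90 = 1294, or 647 per arm. Power for 22% vs 16% is 78.6%, close to an assumed 80% (the SAP states no power for this outcome). With 636 per arm and no missing data it is 77.9%.

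**Shrinkage, no informative auxiliary.** A fraction 1 - f of each arm shows the true difference and a fraction f shows none, so the expected RD is RD x (1 - f).
- 5%: -6 x 0.95 = -5.7
- 19.3%: -6 x 0.807 = -4.8
- 30%: -6 x 0.70 = -4.2

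**Shrinkage with an informative auxiliary.** If an auxiliary measured after randomisation has squared correlation R2 with the outcome and is observed for everyone, it passes on a share R2 of the effect. The expected RD is then RD x [1 - f(1 - R2)]. Assume sensitivity 0.7 and specificity 0.9 for asthma ever, with overall prevalence 0.19.
- P(auxiliary positive) = 0.19 x 0.7 + 0.81 x 0.1 = 0.214
- R2 = (0.19 x 0.81 x 0.6)^2 / (0.19 x 0.81 x 0.214 x 0.786) = 0.33
- 19.3%: -6 x (1 - 0.193 x 0.67) = -5.2
- 30%: -6 x (1 - 0.30 x 0.67) = -4.8

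**Standard errors, group omitted, no auxiliary.** Let V be the full-data variance: (0.22 x 0.78 + 0.16 x 0.84)/636 = 0.000481, so the SE is 2.19 points. The estimate is in effect (1 - f) times the complete-case one, so its true variance is about (1 - f)^2 x V/(1 - f) = (1 - f)V. Rubin's rules report about V within imputations plus fV between them, or (1 + f)V. The reported SE is too large by the factor sqrt[(1 + f)/(1 - f)].
- 19.3%: sqrt(1.193/0.807) = 1.22
- 30%: sqrt(1.30/0.70) = 1.36. Under the null the 95% interval covers P(|Z| < 1.96 x 1.36) = 99%.

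**Power.** At 19.3% missing with group omitted, the reported SE is sqrt(1.193) x 2.19 = 2.40 points and the significance threshold is 1.96 x 2.40 = 4.70. The true SE is sqrt(0.807) x 2.19 = 1.97. Power = P(Z > (4.70 - 4.84)/1.97) = 53%. With group included and no auxiliary, power is close to that of a complete-case analysis.

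| Missing | Expected RD, group omitted | Power, omitted | Power, included |
|---|---|---|---|
| 5% | -5.7 | 73% | 76% |
| 19.3% | -4.8 | 53% | 69% |
| 30% | -4.2 | 35% | 63% |

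**Simulation check** (22% vs 16%, 637/635, Rubin pooling, no auxiliary). With 600 replicates and 30 imputations, group omitted gave -4.8 points and 53% power at 19.3% missing, and -4.3 and 35% at 30%. Group included gave -6.1 with 69%, and -6.1 with 64%. With the assumed auxiliary fully observed and group omitted, the means were -5.2 and -4.8. A separate run of 300 replicates and 10 imputations gave, with group omitted and no auxiliary, -5.7, -5.0 and -4.2 at 5%, 19.3% and 30% (Monte Carlo SE about 0.1 point).

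**The case against.** **The list may not be exhaustive.** The tabulated variables are ones that may be included, they are described as informed by a causal diagram that is not reproduced in the text at hand, and the authors may take treatment group for granted. This stands in part: the document does not prove that the analysis will be run without group. But the governing sentence says what will be in the model, and it justifies the omission of two strata without mentioning allocation. Section 5.1 has the SAPs finalised and made public before full unblinding, so this term should not be left to inference.

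**A reader might infer that the imputed values carry no treatment effect at all.** The SAP does not support that. Evidence of asthma at 36 or 48 months, bronchiolitis hospitalisation in the first year and atopy at one year all follow randomisation and can pass on part of an effect. The fraction missing is therefore a ceiling on the shrinkage. Children who never entered Part 2 would lie nearer that ceiling, because they would have no 36- or 48-month data.

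**A reader might take 19.3% as the minimum missing for the primary outcome.** It is not. Under section 4.2 a no on the 7-10 year questionnaire is a valid negative, and section 4.1.3 sends that questionnaire to participants with missing data. Whether families outside Part 2 received it is not stated. Such answers could lower the figure, and later non-response could raise it.

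**A reader might infer that secondary outcomes are left out of the imputation.** Section 5.2.3 speaks of models, in the plural, for the outcome variables, which largely answers this. Only a wording note remains.

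**Conclusion.** The point holds as a defect in the specification: randomised group is absent from the stated imputation model, while every arm comparison, including the primary one, rests on the imputed data. The bias is conditional on the model being run as listed. Its direction is then toward zero, with intervals that are too wide.

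For a true -6 points, the loss ranges from about 0.3 points at 5% missing to 1.2 at 19.3% and 1.8 at 30% without an informative auxiliary. With the assumed, fully observed auxiliary it is about 0.8 at 19.3% and 1.2 at 30%. At 19.3% missing and no auxiliary, power falls from about 70% to about 53%.

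These figures assume outcomes missing completely at random and the planning rates of 22% and 16%. The actual fraction missing and the strength of the auxiliaries are not in the SAP. Because the primary estimate is affected and the remedy is trivial, this should be settled before unblinding.

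**What to change.** In section 5.2.3, state that imputation is run separately by randomised group. This is preferable because it also preserves the intervention-by-subgroup interactions of section 5.2.4, which a main-effect term for group would not. At minimum, state that randomised group is a predictor in every imputation equation; that is enough for the main-effect risk differences in 5.3 and 5.4.

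As a wording note only, make explicit that each secondary outcome is in the imputation model used for its own analysis.

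The cost is one or two sentences of SAP text and one option in the imputation code. No new data are needed.

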#### 4.1.2. ISAAC questions at five years of age

At five years of age the questionnaires included validated questions from the International Study of Asthma and Allergies in Childhood (ISAAC).

These questions are:

1. *Has your child ever had wheezing or whistling in the chest at any time in the past?*  
*Yes/No/Don't know*

If they answer yes to the first question, the following question was asked:

2. *Has your child had wheezing or whistling in the chest in the past 12 months?*  
*Yes/No/Don't know*

If they answer yes to this question, the following questions were asked:

3. *How many attacks of wheezing has your child had in the past 12 months?*  
*None | 1 to 3 | 4 to 12 | More than 12*
4. *In the past 12 months, how often, on average, has your child's sleep been disturbed due to wheezing?*  
*Never woken with wheezing | Less than one night per week | One or more nights per week*
5. *In the past 12 months, has wheezing ever been severe enough to limit your child's speech to only one or two words at a time between breaths?*  
*Yes/No*

All participants were asked:

6. *Has your child ever had asthma?*  
*Yes/No/Don't know*
7. *In the past 12 months, has your child's chest sounded wheezy during or after exercise?*  
*Yes/No*
8. *In the past 12 months, has your child had a dry cough at night, apart from a cough associated with a cold or chest infection?*  
*Yes/No*

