#### 4.1.4. Asthma medication

Preventer and reliever medication are commonly prescribed to children for wheeze and asthma. Whereas relievers are prescribed in acute phases, to relieve acute symptoms, preventers are prescribed for more severe asthma, to decrease inflammation and prevent episodes.

In the five-year questionnaire, if the parent/guardian indicated that the child had either asthma or wheezing, the parent/guardian was asked whether the child had ever used any medication, pills, puffers or other medicines for wheezing or asthma. If yes, they were presented a list of medications that included:

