## 4.2. PRIMARY OUTCOME

### 1. Asthma ever, defined by ISAAC questions

**Positive** if the parent/guardian answered 'yes' to 'Has your child ever had asthma?' (ISAAC Q6).

**Negative** if the parent/guardian answered

- 'no' to 'Has your child ever had asthma' in the 5-year questionnaire (ISAAC Q6).
- OR
- 'no' to the asthma question in the 7 – 10-year follow-up questionnaire

**Missing** if in the 5-year questionnaire the response to ISAAC Q6 is missing or don't know AND the response to the follow-up questionnaire is not 'no'.

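### The listed imputation variables include no five-year wheeze or medication answer, so asthma ever can be imputed without answers the parent may have given in the same questionnaire

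*SAP*

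**What the plan says.** Section 5.2.3 (Multiple Imputation) states what enters the model: "The primary outcome, strata variable (mode of birth: vaginal/caesarean), and the variables associated with either remaining in the study or asthma listed below". The list is ordered by priority and is permissive: "the variables listed below may be included in the multiple imputation". Nothing says that unlisted variables may be added.

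The one listed variable that records asthma symptoms after infancy is 'Evidence of asthma': "Positive if parent reported asthma or wheeze disturbing sleep or exercise at 36 or 48 months or said yes on the follow-up questionnaire". It draws on the 36- and 48-month questionnaires and the 7-10-year follow-up, not on the five-year questionnaire.

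Under section 4.2, asthma ever is missing when "the response to ISAAC Q6 is missing or don't know AND the response to the follow-up questionnaire is not 'no". Such a child is then imputed.

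The five-year questionnaire asks about wheeze separately from Q6. Q1 (section 4.1.2) is "Has your child ever had wheezing or whistling in the chest at any time in the past", and a 'yes' leads to Q2 and then to Q3-Q5. Q7 and Q8 go to all participants. Under section 4.1.4, a parent who indicated either asthma or wheezing "was asked whether the child had ever used any medication, pills, puffers or other medicines for wheezing or asthma", and then about use in the last 12 months.

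Section 5.4 adds: "Intention to treat analysis with multiple imputation will be used for all the secondary outcomes". It does not say whether this happens in one chain with the primary outcome or in separate models.

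**The concern.** A parent can be unsure whether the child has ever had asthma and still report current wheeze and a preventer. Read as listed, the model cannot tell that child from a never-wheezer with the same earlier history. Uncertainty about the label is plausibly commonest where a child wheezes without a firm diagnosis. If so, missing at random is more credible given five-year wheeze than without it, and the most informative answers on these children go unused.

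At stake are the level of asthma ever, some precision, and the coherence of the imputed outcomes. Current asthma requires Q6 'yes', and ISAAC severity requires current wheeze. Separate imputation can produce current asthma without asthma ever, or severe asthma without current wheeze.

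**Working it through.** **Step 1: the list against the five-year items.** The 16 variables are maternal education, daycare, smoke exposure, sex, breastfeeding, family history of asthma, pets, delivery mode (also the stratum variable), season of birth, maternal age, paternal age, low birthweight, timing of recruitment, evidence of asthma, bronchiolitis hospitalisation in year one, and atopy at one year. Variables using Q1-Q5, Q7, Q8 or the five-year medication section: 0 of 16.

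**Step 2: which outcomes are affected when Q6 is unknown and there is no follow-up 'no'.**
- Asthma ever (4.2): missing, so imputed.
- Current asthma (4.3, item 1): Q1 'no', or Q1 'yes' with Q2 'no', already makes it negative. With definite wheeze answers it stays missing only where Q1 and Q2 are both 'yes'.
- Current wheeze (4.3, item 2): the positive and negative rules use only Q1 and Q2, but the missing rule also names Q6. A blank Q6 could therefore remove a known wheeze status.
- ISAAC severity and preventer use (items 3 and 4): classified mainly from Q1-Q5 and the medication answers, so an unknown Q6 need not make them missing.

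**Step 3: size, first illustration.** The SAP gives no count of 'don't know' answers and no figure to reproduce. Inputs from the SAP: 1272 randomised and 1027 in Part 2 (2.1); 22% asthma ever and a 6-point design difference (2.4). Assumed: affected children are k = 10, 31 or 51 (1%, 3% or 5% of 1027); their true risk p given the five-year answers is 5% to 80%; they are imputed at about 22%.

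Error in pooled risk = k × (0.22 - p) / 1272.

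| k | p = 0.05 | p = 0.80 |
|---|---|---|
| 10 | +0.13 points | -0.46 points |
| 31 | +0.41 | -1.41 |
| 51 | +0.68 | -2.33 |

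Error in the risk difference, with equal p in both arms and about 636 children per arm = (k in one arm - k in the other) × (0.22 - p) / 636.
- Even split: 0.
- 51 children split 31 and 20, p = 0.80: 11 × 0.58 / 636 = 1.0 point in size.
- All in one arm, p = 0.80: 0.9, 2.8 and 4.7 points for k = 10, 31 and 51. This is a bound, not an expectation.

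**Step 4: second illustration, with earlier evidence in the model.** Assumed: 916 responders; 2-6% 'don't know' (18-55 children); current wheeze 18%; asthma risk 60% in wheezers; 36/48-month evidence in 50% of wheezers and 12% of others. Only the 22% comes from the SAP.
- Risk in non-wheezers: (0.22 - 0.18 × 0.60) / 0.82 = 0.137.
- Evidence present overall: 0.18 × 0.50 + 0.82 × 0.12 = 0.188. Risk is 0.358 with evidence and 0.188 without.
- Imputed risk, wheezer: 0.50 × 0.358 + 0.50 × 0.188 = 0.273, against 0.60.
- Imputed risk, non-wheezer: 0.12 × 0.358 + 0.88 × 0.188 = 0.208, against 0.137.
- Cases lost per child if a share w wheeze: 0.327w - 0.071(1 - w), which is 0.088 at w = 0.4 and 0.208 at w = 0.7.
- Total: 18 × 0.088 = 1.6 up to 55 × 0.208 = 11.4, so about 2-11 cases, or 0.1-0.9 points of 1272.

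**The case against.** The best reply is that section 5.2.3 speaks of imputation models for the outcome variables, in the plural, by chained equations, and section 5.4 imputes every secondary outcome. If all outcomes sit in one chain, current wheeze, severity and preventer use do inform asthma ever. That reading is possible, so one cannot say that the SAP rules these answers out. But the next sentence of 5.2.3 names only the primary outcome, and a joint chain is nowhere stated. Even a joint chain of the defined outcomes would omit reliever use, Q7 and Q8.

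Other objections stand in part:
- A reader might infer that these children are imputed as if nothing were known about their asthma. They are not. Reports at 36 and 48 months and a follow-up 'yes' are used, and a follow-up 'no' settles the outcome without imputation. Because such reports are nearly direct evidence of asthma ever, the second illustration, which treats them as uninformative once wheeze is known, probably overstates the loss.
- Q1 and Q2 also allow 'don't know', so the parent may, but need not, have given usable wheeze answers.
- The stated aim is to impute children who did not remain in the study. At least 1272 - 1027 = 245 never entered Part 2, and five-year answers cannot help them directly. Reading the omission as a breach of the plan's own selection rule goes too far, although the section also mentions incomplete data.
- Branched items can cause perfect prediction, and the plan already expects to collapse categories so that the imputation runs.

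**Conclusion.** The point holds in limited form. As listed, the model uses no five-year wheeze or medication answer, and the SAP leaves open whether the outcomes are imputed jointly. It concerns only five-year responders with Q6 unknown and no follow-up 'no'. Their number is not given and may be small.

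The main effect is on the pooled risk and on precision: about 0.1-0.9 points too low in the second illustration, and +0.7 to -2.3 points under the wider assumptions. Every input other than 22%, 1027 and 1272 is assumed.

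A reader might infer that the treatment effect is biased. The document does not support that. The reported effect is the risk difference (5.3), which is biased only if these answers differ by arm. Parents are not blinded (2.2), so this is possible, but nothing shows that it occurs. Nor are all secondary outcomes compromised: among children with definite wheeze answers, current asthma is affected only where Q1 and Q2 are 'yes' and Q6 is unknown. Conflicting imputed values arise only if outcomes are imputed separately.

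It is worth correcting because the data are in hand and the change is small. It does not by itself undermine the primary comparison.

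**What to change.** In section 5.2.3, state that asthma ever is imputed jointly with five-year current wheeze and 12-month preventer use. Take current wheeze from Q1 and Q2 as answered, whatever the status of Q6. Add 12-month reliever use, Q7 and Q8 as auxiliary variables if the model converges. Derive current asthma and severity so that they agree with their definitions in section 4.3: current asthma implies asthma ever, and ISAAC-defined severe asthma implies current wheeze. If one joint chain was always intended, say so. Report the number of children with Q6 'don't know' or blank, by arm.

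The cost is SAP wording, modest programming and a slightly larger model with some risk of perfect prediction from the branched items. No new data are needed. Children with no five-year questionnaire gain nothing directly. Full item-by-item conditional imputation in questionnaire order is optional.
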